#### Cohort study

The primary endpoint (percentage of subjects staying peanut tolerant) will be reported as absolute number and percentage with the corresponding 95% confidence interval. Other endpoints will be summarized descriptively. Explorative comparisons of endpoints vs. baseline values will be performed (with methods for paired data). Further details will be described in the SAP.

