**Methods:**

The TINA trial consisting of (part I) a randomized, controlled, open, parallel group, single-center, superiority trial (RCT), and (part II) a prospective observational exploratory cohort study. Children and adults (age 1–67 years) with suspected or known primary PN and/or TN allergy will undergo an oral food challenge (OFC) to determine their clinical reactivity and individual threshold. In the RCT, 120 PN or TN allergic patients who tolerate ≥100 mg of food protein will be randomized (1:1 ratio) to consumption of products with low amounts of PN or TN on a regular basis or strict avoidance for 1 year. The consumption group will start with 1/100 of their individual threshold, increasing the protein amount to 1/50 and 1/10 after 4 and 8 months, respectively. The primary endpoint is the clinical tolerance to PN or TN after 1 year assessed by OFC. In the cohort study, 120 subjects sensitized to PN and/or TN but tolerant are advised to regularly consume the food and observed for 1 year. The primary endpoint is the maintenance of clinical tolerance to PN and/or TN after 1 year assessed by challenging with the former tolerated cumulative dose.

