#### Exclusion criteria

• Other severe diseases (cardiac, cystic fibrosis, congenital)

• Participation in another interventional trial that requires consumption of food protein

• Immunotherapy or therapy with biologicals for the treatment of food allergy in the past 12 months

• Uncontrolled asthma

• Usage of antihistamines 3–5 days before OFC

• Therapy with beta-blocker and/or ACE inhibitors

• Systemic immunosuppression

• Pregnancy or lactation

Further exclusion criterion for the RCT is an allergic reaction to less than the 5th dose of peanut or tree nut protein on OFC at screening. The 5th dose is around 300 mg depending on the individual allergen. Dose steps and the corresponding allergen amounts used for OFCs with peanut or individual tree nuts are displayed in Appendix of the full protocol.

Another exclusion criterion for the cohort study is a positive OFC with peanut and/or tree nut at screening.

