#### Cohort study

The primary endpoint is the maintenance of clinical tolerance to peanut and/or tree nuts after 1 year assessed by feeding of the former tolerated cumulative dose.

Clinical tolerance is defined as the absence of allergic symptoms other than subjective symptoms or mild erythema, oral pruritus, mild nausea, mild abdominal pain, mild rhinitis, and/or less than three perioral hives during OFC or supervised feeding of the repetitive cumulative peanut and/or tree nut dose according to PRACTALL guidelines [32].

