#### Cohort study

Maintenance of clinical tolerance to peanut after 1 year assessed by feeding of the former tolerated cumulative dose in % of peanut-allergic patients.Maintenance of clinical tolerance to tree nuts after 1 year assessed by feeding of the former tolerated cumulative dose in % of tree nut-allergic patients.Maintenance of clinical tolerance to individual tree nuts after 1 year assessed by feeding of the former tolerated cumulative dose in % of the respective type of tree nut-allergic patients.Change in peanut- and/or tree nut-specific wheal size as well as IgE and IgG4 at 12 months from baseline.Dietary compliance (frequency and amount of peanut and/or tree nut consumption) during the study, assessed by questionnaires, telephone interviews, and during clinical visits.Frequency of allergic reactions to the food (peanut and/or tree nut) that was advised to consume regularly or to other food allergens during the observational period assessed by questionnaires during telephone interviews and clinical visits.In participants with atopic dermatitis: change of severity of atopic dermatitis (SCORAD, EASI) and topical eczema treatment at 12 months from baseline.Use of epinephrine as a rescue medication during the study.Change in generic and disease-specific quality of life during and after the study from baseline assessed by questionnaires (PedsQL, EQ-5D, FAQLQ, FAIM).Eating habits assessed by questionnaires at baseline compared to during and after the study.Burden of dietary behavior at two time points during the intervention assessed by a visual analog scale.

Non-compliance of the liberated diet group is defined as a repeated event of insufficient consumption of small allergen amounts, i.e., < 2 times per week for three weeks (either during 3 consecutive weeks or three repeated events of 1 week). Non-compliance of the strict avoidance group is defined as a repeated event of intended consumption of the specific allergen, i.e., > 3 times during the study period.

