Since many patients with peanut allergy have an allergy to tree nut in parallel, a strength of our study is the inclusion of patients with peanut and/or tree nut allergy. While in part I, the RCT, for practical and safety reasons, only one allergen (peanut, hazelnut, cashew or walnut) will be part of the intervention, in part II (the cohort study) we observe tolerant participants regarding all foods (peanut, hazelnut, cashew and walnut) they exhibited tolerance upon OFC. As primary peanut and tree nut allergy is rarely outgrown, a further strength is that we included patients of all age groups.

The results of the trial will be submitted for publication in peer-reviewed journals and will further be communicated to participants, health care providers, especially allergologists, as well as dieticians and nutritionists specialized in food allergy to further improve the management of peanut and tree nut allergy, as they may affect current dietary recommendations.

To summarize, the objective of this randomized trial is to investigate whether there is a better option than strict avoidance diet for the management of peanut and tree nut allergy. This clinical trial will help to determine the impact of allergen avoidance on natural tolerance development and whether the current dietary advice for peanut or tree nut-allergic patients with higher threshold levels is still valid. Our results would help to provide better and individualized recommendations for patients with peanut and tree nut allergy. Furthermore, in a large prospective observational cohort, we will assess compliance of the dietary recommendation regarding introduction and regular consumption of peanut and tree nut in challenge-proven tolerant children and adults and its impact on maintenance of tolerance.

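### The analysis sentence for the cohort's primary endpoint covers peanut only, although the endpoint is defined for peanut and/or tree nuts, and three cohort secondary endpoints use a denominator of allergic patients that does not fit a tolerant cohort

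*Protocol article*

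**What the plan says.** The protocol article defines the cohort's primary endpoint in two places, and they agree. The Abstract (Methods) has "The primary endpoint is the maintenance of clinical tolerance to PN and/or TN after 1 year", and the Primary endpoint section has "The primary endpoint is the maintenance of clinical tolerance to peanut and/or tree nuts after 1 year". The Discussion supports this scope, saying that "in part II (the cohort study) we observe tolerant participants regarding all foods" they tolerated at challenge, and it names peanut, hazelnut, cashew and walnut.

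The Planned analysis section for the cohort states the endpoint differently: "The primary endpoint (percentage of subjects staying peanut tolerant) will be reported as absolute number and percentage", together with a 95% confidence interval. Other cohort endpoints are to be summarized descriptively, and further detail is left to the SAP.

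The cohort's secondary endpoints begin with three allergen-specific versions of the same outcome: peanut, tree nuts as a class, and each tree nut. The first reads "Maintenance of clinical tolerance to peanut after 1 year assessed by feeding of the former tolerated cumulative dose in % of peanut-allergic patients". The other two use the corresponding tree nut-allergic denominators.

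On who is in the cohort, the Exclusion criteria say: "Another exclusion criterion for the cohort study is a positive OFC with peanut and/or tree nut at screening". The Study procedures section enrols into the cohort only subjects with a negative challenge who tolerated the repetitive cumulative dose. The Participants section, by contrast, describes the populations of both parts as having challenge-proven allergy.

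**The concern.** An endpoint should have one definition, and the analysis sentence is where it becomes a numerator and a denominator. Here that sentence drops the tree nut component.

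Three things follow if it is applied as written. A subject who entered on a tree nut alone has no value for the headline outcome. A subject who keeps peanut tolerance but loses hazelnut tolerance counts as a success in it. And the primary result becomes the same quantity as the first secondary endpoint, so the endpoint that was actually defined has no stated analysis.

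The denominators raise a related problem. A percentage of allergic patients suits the randomized trial, but a person allergic to a food at entry has no tolerance to that food to maintain.

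At stake is the main descriptive result of part II: which foods it covers, which subjects it counts, and whether that choice is settled before the data are seen.

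**Working it through.** The plan gives no figure to reproduce for this point. The cohort has no formal sample size calculation, no expected maintenance rate and no stated peanut share. The check is therefore mainly a comparison of texts, with arithmetic for illustration only.

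**1. Scope of the primary endpoint**

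| Place in the protocol article | Foods covered |
|---|---|
| Abstract, Methods | peanut and/or tree nuts |
| Objectives, part II | peanut or tree nut allergy; tolerance to peanut and/or tree nut |
| Primary endpoint, Cohort study | peanut and/or tree nuts |
| Study procedures, Cohort study (feeding at visit 4) | peanut and/or tree nut |
| Discussion | all foods tolerated at challenge |
| Planned analysis, Cohort study | peanut only |

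The last row is the exception, and it is the only place that says how the endpoint will be analysed.

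**2. Denominators of the secondary endpoints**

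The denominators of the first three cohort secondary endpoints match those of the first three secondary endpoints of the randomized trial. There they fit, because trial participants have a positive challenge. In the cohort they conflict with the exclusion criterion and the entry rule. The same outcome line refers to "feeding of the former tolerated cumulative dose in % of peanut-allergic patients": a dose formerly tolerated, in patients called allergic.

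**3. Effect on precision (assumed rate and shares)**

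Inputs: n = 120 from the Sample size calculation section; 90% maintenance, assumed; 80, 60 or 40 subjects with a peanut result, assumed. The exact (Clopper-Pearson) limits for x maintaining out of n are the 2.5% quantile of Beta(x, n - x + 1) and the 97.5% quantile of Beta(x + 1, n - x).

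| Subjects counted | x/n | Exact 95% CI | Width (points) |
|---|---|---|---|
| 120 | 108/120 | 83.2-94.7% | 11.5 |
| 80 | 72/80 | 81.2-95.6% | 14.3 |
| 60 | 54/60 | 79.5-96.2% | 16.7 |
| 40 | 36/40 | 76.3-97.2% | 20.9 |

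**4. Effect on the estimate (assumed counts)**

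Suppose 60 subjects entered on peanut and 60 on tree nuts only, and that 57 and 51 of them maintain tolerance.
- Endpoint as defined: (57 + 51)/120 = 108/120 = 90.0%.
- Analysis sentence, peanut subjects only: 57/60 = 95.0%.
- Analysis sentence, all subjects kept in the denominator: 57/120 = 47.5%.

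The sentence does not say which of the last two denominators applies. The gap from 90.0% depends wholly on the assumed counts, but it shows that the wording can move the estimate as well as its precision.

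**The case against.** The strongest reply is that this is a slip in a parenthesis. The rest of the article covers tree nuts, the visit 4 feeding collects the data under either reading, the article is abridged, and the SAP is still to come. Much of this stands: a careful reader can tell what was probably meant, and nothing is lost if the text is corrected in time. But abridgement and deferral to the SAP explain what is left out. They do not settle two conflicting statements that are both printed, and an SAP author could follow either.

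A reader might infer that tree nut losses would go uncounted. The document does not support that. The second and third secondary endpoints report maintenance of tolerance to tree nuts and to each tree nut, so such losses are missing from the headline figure only.

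It can also be said that calling the denominators empty is over-literal. Subjects enter with suspected or known allergy, so the wording may be a loose label, probably carried over from the randomized trial's list. That is fair as to intent. The label is still wrong for subjects admitted on a negative challenge.

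Finally, the defined endpoint does not say how a subject tolerant to several foods is scored. Requiring tolerance to every food would be a new rule, not a correction, and an exact interval is one choice among several. Both points stand, and the fix below is limited accordingly.

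**Conclusion.** The inconsistency holds on the text alone and rests on no assumption. The analysis sentence for the cohort's primary endpoint is narrower than the endpoint it names, and the first three cohort secondary endpoints have denominators that do not describe the cohort. The Participants section makes the same population error.

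The numerical size is uncertain, because it depends on a peanut share and a maintenance rate that the document does not give. Over the range shown, the loss of precision is modest to moderate. The more important matter is which foods and subjects the headline figure represents.

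The severity is moderate. A reader might take this as undermining the trial's main conclusion. It does not: the cohort is labelled exploratory, its primary endpoint is reported descriptively without a planned hypothesis test, and the analysis of the randomized trial is untouched.

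**What to change.** 1. In Planned analysis, Cohort study, replace the parenthesis with the percentage of subjects maintaining tolerance to peanut and/or tree nuts, as defined in the Primary endpoint section.
2. Have the authors state, before analysis, how a subject tolerant to several foods is counted. Tolerance kept to every food tolerated at entry is one possible rule; the choice is theirs.
3. In the first three cohort secondary endpoints, change the denominators to subjects tolerant at the entry challenge to peanut, to tree nuts, and to the respective tree nut.
4. In Participants, correct the sentence that describes both populations as challenge-proven allergic, so that the cohort is described as sensitized but tolerant.

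The cost is a text correction, carried into the full protocol and the SAP if they contain the same wording. No new data, visits or subjects are needed.

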## Discussion

Primary peanut and tree nut allergy is rarely outgrown and, therefore, affects both children and adults. Up to now, strict allergen avoidance is recommended for patients with peanut and tree nut allergy, independently of their individual threshold level, whereas sensitized subjects with challenge-proven tolerance are advised to introduce the food in the diet and consume it on a regular basis. As a strict elimination, diet has a negative impact on the everyday life of patients, effective strategies to prevent persistent food allergy other than the current management recommendation of strict avoidance would be of major importance. This clinical trial, including 120 children and adults with challenge-proven peanut and/or tree nut allergy reacting at higher threshold doses (RCT, part I) and 120 sensitized subjects with tolerance to peanut and/or tree nut (cohort study, part II), will investigate whether a liberated diet compared to strict avoidance can prevent the persistence of peanut and tree nut allergy and whether regular consumption of peanut and/or tree nut prevents (re-)development of peanut and tree nut allergy.

To our knowledge, this is the first ongoing trial investigating a novel dietary management option with a liberated diet (consumption of sub-threshold allergen amounts using small servings of store-bought products containing peanut or tree nut) compared to strict avoidance for peanut- and tree nut-allergic children and adults with higher threshold levels. Next to our trial, the ongoing CAFETERIA study in the US investigates a similar approach in children with peanut allergy reacting only to higher amounts of peanut (registered on ClinicalTrails.gov, NCT03907397). This trial aims to include 98 children between 4 and 14 years of age with challenge-proven peanut allergy able to ingest at least 143 mg of peanut protein. Children are randomized either to ingestion of sub-threshold amounts of peanut in their diet depending upon their reaction threshold (using store-bought peanut butter) or standard care of strict avoidance.

Since many patients with peanut allergy have an allergy to tree nut in parallel, a strength of our study is the inclusion of patients with peanut and/or tree nut allergy. While in part I, the RCT, for practical and safety reasons, only one allergen (peanut, hazelnut, cashew or walnut) will be part of the intervention, in part II (the cohort study) we observe tolerant participants regarding all foods (peanut, hazelnut, cashew and walnut) they exhibited tolerance upon OFC. As primary peanut and tree nut allergy is rarely outgrown, a further strength is that we included patients of all age groups.

The results of the trial will be submitted for publication in peer-reviewed journals and will further be communicated to participants, health care providers, especially allergologists, as well as dieticians and nutritionists specialized in food allergy to further improve the management of peanut and tree nut allergy, as they may affect current dietary recommendations.

To summarize, the objective of this randomized trial is to investigate whether there is a better option than strict avoidance diet for the management of peanut and tree nut allergy. This clinical trial will help to determine the impact of allergen avoidance on natural tolerance development and whether the current dietary advice for peanut or tree nut-allergic patients with higher threshold levels is still valid. Our results would help to provide better and individualized recommendations for patients with peanut and tree nut allergy. Furthermore, in a large prospective observational cohort, we will assess compliance of the dietary recommendation regarding introduction and regular consumption of peanut and tree nut in challenge-proven tolerant children and adults and its impact on maintenance of tolerance.

## Trial status

This is an abridged protocol based on protocol version 5.0 dated 09 September 2021. The first patient was randomized in March 2020 and the last patient is planned to be enrolled in the third quarter 2022.

## Data Availability

All data generated in the CRU will be curated and organized into a set of files, shared on an online, publicly available data repository after peer-reviewed publication (preservation and accessibility of the data) to ensure potential secondary analyses, long-term archiving, and reuse by other researchers (scientific recognition). Besides the study protocol, publications are planned for the results in peer-reviewed journals. In addition, results will be communicated in lay language to participants and health care providers as they may affect current dietary recommendations for patient with peanut and or tree nut allergy.

## Abbreviations

ANCOVA: Analysis of covariance
BIH: Berlin Institute of Health
CRF: Case Report Form
CRU: Clinical research unit
DBPCFC: Double-blind Placebo-Controlled Food Challenge
DFG: German Research Foundation
EASI Score: Eczema Area and Severity Index Score
eCRF: Electronic Case Report Form
EMA: European Medicines Agency
EQ-5D: European Quality of Life 5 Dimensions
FAIM: Food allergy independent measure
FAQLQ: Food Allergy Quality of Life Questionnaire
FAS: Full Analysis Set
FDA: Food and Drug Administration
IgE: Immunoglobulin E
IgG4: Immunoglobulin G4
LEAP trial: Learning Early About Peanut trial
OFC: Oral Food Challenge
PC: Phone Call
PedsQL: Pediatric Quality of Life Inventory
PEESS: Pediatric Eosinophilic Esophagitis Symptom Score
PN: Peanut
PP: Per-Protocol
PRACTALL: PRACTical issus of ALLergology, Joint United States/European Union Initiative
REC: Research Ethics Committee
REDCap: Research Electronic Data Capture
NaCl: Sodium chloride
SAE: Serious adverse event
SAP: Statistical Analysis Plan
SCORAD: SCORing Atopic Dermatits
SPT: Skin Prick Test
SPIRIT: Standard Protocol Items: Recommendations for Interventional Trials
TEWL: TransEpidermal Water Loss
TINA: Tolerance Induction through Non-avoidance to prevent persistent food Allergy
TN: Tree Nut
UK: United Kingdom
V: Visit
